### Blinding

The patient, investigator and the treating physician at the outpatient clinic are blinded for the treatment allocation (BMS or CS). For the duration of the trial the allocated stent will not be disclosed unless there is a medical need (i.e., restenosis, stent fracture).

### Sample size

The sample size calculation for this randomized controlled, superiority trial is based on the retrospective data of Oderich et al. [21]. Assuming that CS improves the patency rate of BMS after 24 months from 63% to 95%, and accounting for a 20% dropout rate, 42 participants are required per arm to achieve 80% power with a two-sided alpha of 0.05. The sample size calculation is performed using the Comparison of Independent Proportions Test (SAS Power and Sample size, SAS Institute Inc., Cary, NC, USA).

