### Statistical methods

Descriptive analyses will be provided regarding patient characteristics before randomization. Because this is a randomized controlled trial, statistical tests to detect differences in these baseline characteristics between both intervention arms will not be performed. The following patient characteristics before randomization will be provided: age, gender, Body Mass Index (BMI), smoking status, comorbidity with hypertension, dyslipidemia, diabetes and cardiovascular disease. Furthermore presenting symptoms will be described as abdominal pain, postprandial pain, exercise-related pain, nausea, diarrhea, weight loss and symptom duration. Patient characteristics will be described as numbers and percentages for dichotomous variables, or as means and standard deviations for continuous variables with normal distribution or medians and interquartile ranges (IQRs) for continuous variables if not normally distributed.

The primary analysis will be performed according the intention-to-treat principle. A per-protocol analysis will also be performed for the primary outcome of stent patency for those patients who were treated according to the treatment protocol.

The primary endpoint of stent patency will be analyzed with a “two-sample z-test” for comparison of two proportions. Furthermore, a predictive model for time-to-event will be obtained by proportional hazards regression and Kaplan-Meier analysis to compare patency rates of CS versus BMS. All other continuous outcome measures will be reported as difference in mean improvement between the CS versus the BMS group. Change in quality of life assessed by the validated questionnaires EQ-5D-5 L [26, 27] and SF-36 [28, 29] will be compared between the CS and BMS groups. Furthermore, the costs of both groups will be compared. All costs will be estimated based on actual input in terms of resource use, personnel and indirect costs from loss of productivity assessed by the cost-effectiveness questionnaire.

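### The sample size of 42 per arm does not follow from its printed inputs: the planned z-test needs 32 per arm for 80% power, and 42 per arm gives about 91%

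*Protocol article*

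**What the plan says.** The Sample size section of the protocol article gives a full set of inputs and a result:

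- Rates: "Assuming that CS improves the patency rate of BMS after 24 months from 63% to 95" per cent.
- Loss, error rates and result: "accounting for a 20% dropout rate, 42 participants are required per arm to achieve 80% power with a two-sided alpha of 0.05".
- Method: "The sample size calculation is performed using the Comparison of Independent Proportions Test".

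Statistical methods names the primary test: "The primary endpoint of stent patency will be analyzed with a “two-sample z-test” for comparison of two proportions". Allocation is 1:1 (Randomization), the total is 84 (Abstract and Trial status), and no interim analysis is planned (Data monitoring). The article mentions no continuity correction, further margin or other inflation.

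**The concern.** A difference of 32 percentage points is large, and 42 per arm looks like too many patients for 80% power to detect it, even after a 20% loss. If the figure does not follow from the inputs, a reader cannot tell what the trial was designed to detect. The section implies that 32 points is the smallest difference found with 80% power, whereas on the printed inputs 84 patients can detect a somewhat smaller one. This has some weight because the assumed rates come from retrospective data, so the true difference may be smaller than assumed.

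**Working it through.** **Inputs (all from the protocol article).** p1 = 0.63, p2 = 0.95, difference 0.32, mean rate 0.79; two-sided alpha 0.05 (z = 1.960); 80% power (z = 0.8416); 20% dropout; 1:1 allocation; stated result 42 per arm.

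**1. Attempt to reproduce 42 with the planned z-test.**

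n = [z(alpha/2) × √(2 × p̄ × (1 − p̄)) + z(power) × √(p1(1 − p1) + p2(1 − p2))]² / (p2 − p1)²

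- √(2 × 0.79 × 0.21) = 0.5760, times 1.960 = 1.1290
- √(0.63 × 0.37 + 0.95 × 0.05) = 0.5297, times 0.8416 = 0.4458
- n = (1.1290 + 0.4458)² / 0.1024 = 2.480 / 0.1024 = 24.2, so 25 evaluable per arm
- with dropout: 25 / 0.80 = 31.25, so 32 randomised per arm, 64 in total

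The stated figure is not reproduced.

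**2. Other standard methods at 80% power, two-sided 0.05, loss applied as n / 0.80.**

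| Method | Evaluable per arm | Randomised per arm |
|---|---|---|
| z-test, unpooled variance | 22 | 28 |
| Arcsine | 22 | 28 |
| z-test, pooled variance under the null (step 1) | 25 | 32 |
| z-test, pooled variance in both terms | 26 | 33 |
| Fisher's exact, full enumeration (28 gives 79.5%, 29 gives 81.7%) | 29 | 37 |
| Continuity-corrected z-test (30.1) | 31 | 39 |

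Inflating for loss as n × 1.2, or using a one-sided alpha, gives smaller numbers than these. No method tried reaches 42; the largest is 39.

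**3. Power that 42 per arm gives on the printed inputs.** 42 × 0.80 = 33.6, so 33 to 34 evaluable per arm.

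Power = Φ{[0.32 × √n − 1.1290] / 0.5297}

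- n = 33: Φ(1.339) = 91.0%
- n = 34: Φ(1.391) = 91.8%
- exact binomial enumeration of the z-test: 93.6% and 94.4%
- Fisher's exact test: 88.3% and 89.5%
- with no dropout (n = 42), z-test formula: 96.3%

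**4. Covered-stent rate detectable with 80% power against 63%.**

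- z-test formula, 33.6 evaluable: 91% gives 79.2%, 91.25% gives 80.1%. So about 63% versus 91%, or 28 points.
- Fisher's exact test, 33 and 34 evaluable: 91% gives 71% and 73%; 93% gives 80.3% and 82.0%. So about 63% versus 93%, or 30 points.

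**5. Could one changed input explain 42?** Two examples:

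- Power of 90% with the z-test gives 32 evaluable and 32 / 0.80 = 40 randomised: close, but not 42.
- A total loss of 40% with the z-test at 80% power gives 25 / 0.60 = 41.7, so 42 exactly.

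Neither is stated in the article, so both are conjecture.

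**The case against.** The strongest reply is that the discrepancy is on the safe side. On the printed inputs 42 per arm does reach 80% power, with room to spare; only the word for needing that many is wrong. Type I error, the estimand and the validity of the primary comparison are untouched, and a null result will be read mainly from its confidence interval. All of this stands, and it limits the weight of the point.

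A second reply is that the article condenses a fuller protocol. That would excuse missing detail, such as the exact software option. It does not excuse a complete list of inputs followed by a result that they do not produce.

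A reader might also infer more than the documents support:

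- *That either the power or the test must be the misprint.* This does not follow. The z-test, its continuity-corrected form and Fisher's exact test all miss 42 at 80% power, so changing the test does not mend it. The wrong input could equally be a patency rate, the dropout allowance or an unstated margin.
- *That 90% power was intended.* That gives 40, and nothing in the article says so.
- *That the sizing test and the analysis test differ.* Both sections name a comparison of two proportions, and no mismatch is shown.

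**Conclusion.** The stated sample size and its printed inputs disagree. For 80% power the planned z-test needs 32 per arm (64 in total) against the stated 42 (84 in total), which is 42 / 32 = 1.31 times the requirement. With 42 per arm, power on the printed inputs is about 91% by the z-test formula and 88% to 90% even with Fisher's exact test.

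This rests on taking the 63% and 95% rates, the two-sided 0.05 level and the 20% dropout as printed. Given those, the trial is larger than its stated power requires and is not underpowered. The article does not reveal which input is wrong, so 91% is the consequence of the inputs as printed and not an established description of the intended design. The fault is one of reporting. It is worth correcting because it sits in the central design calculation and overstates the smallest detectable difference by about 2 to 4 points, depending on the test.

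**What to change.** Keep 84 patients; 71 were already enrolled by September 2018 (Trial status), and nothing here argues for changing enrolment. Retrieve the output of the original sample size calculation and compare each input with the printed one. Then do one of two things:

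- If an input was misprinted or left out (power, a patency rate, the loss allowance, a correction or a margin), correct or add it so that 42 follows.
- If the printed inputs are right, restate the result, for example: 42 patients per arm, of whom 33 to 34 are expected to be evaluable after 20% dropout, give about 91% power to detect 63% versus 95% with the two-sample z-test at two-sided 0.05, or 80% power to detect 63% versus about 91% (about 93% if Fisher's exact test is used).

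The cost is one check of a stored calculation and a change of wording.

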### Data collection methods

Clinical data are collected using web-based case record forms (9 Knots Business Solutions Ltd., Mansfield, UK). Quality of life is assessed by the validated EuroQol five-dimension, five-level questionnaire (EQ-5D-5 L) [26, 27] and 36-item Short-Form Health Survey (SF-36) [28, 29] questionnaires. The cost-effectiveness questionnaire deals with work omission, hospital visits and use of healthcare. All trial documents are kept for 15 years after study completion.

### Data management

Data entry is performed by local study personnel or personnel of the initiating study center. Data entry is anonymized replacing all patient names with a code. Only these codes are used as reference in reports and publications about this investigation. The web-based case record forms contain range checks for data values. The handling of personal data is compliant with the Dutch Personal Data Protection Act, the Code of Good Behavior and the General Data Protection Regulation effective since May 2018.

### Data monitoring

Institution of a data monitoring committee (DMC) was waived by the Ethical Committee because the added risk of the interventional study arm is considered to be negligible. An interim analysis will not be performed. The initiating center, Erasmus MC University Medical Center, is responsible for the data monitoring activities to ensure data quality.

### Statistical methods

Descriptive analyses will be provided regarding patient characteristics before randomization. Because this is a randomized controlled trial, statistical tests to detect differences in these baseline characteristics between both intervention arms will not be performed. The following patient characteristics before randomization will be provided: age, gender, Body Mass Index (BMI), smoking status, comorbidity with hypertension, dyslipidemia, diabetes and cardiovascular disease. Furthermore presenting symptoms will be described as abdominal pain, postprandial pain, exercise-related pain, nausea, diarrhea, weight loss and symptom duration. Patient characteristics will be described as numbers and percentages for dichotomous variables, or as means and standard deviations for continuous variables with normal distribution or medians and interquartile ranges (IQRs) for continuous variables if not normally distributed.

The primary analysis will be performed according the intention-to-treat principle. A per-protocol analysis will also be performed for the primary outcome of stent patency for those patients who were treated according to the treatment protocol.

The primary endpoint of stent patency will be analyzed with a “two-sample z-test” for comparison of two proportions. Furthermore, a predictive model for time-to-event will be obtained by proportional hazards regression and Kaplan-Meier analysis to compare patency rates of CS versus BMS. All other continuous outcome measures will be reported as difference in mean improvement between the CS versus the BMS group. Change in quality of life assessed by the validated questionnaires EQ-5D-5 L [26, 27] and SF-36 [28, 29] will be compared between the CS and BMS groups. Furthermore, the costs of both groups will be compared. All costs will be estimated based on actual input in terms of resource use, personnel and indirect costs from loss of productivity assessed by the cost-effectiveness questionnaire.

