### Randomization

Patients are 1:1 randomized for a BMS or CS with a web-based randomization module (9 Knots Business Solutions Ltd., Mansfield, UK) in random blocks of four or six stratified by center.

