### Follow-up

After the endovascular procedure, the patients are followed up at 6, 12 and 24 months with CTA to assess stent patency and with a visit to the outpatient clinic to assess symptoms and bodyweight. The patients also receive questionnaires to assess quality of life and cost-effectiveness before stent placement and 6, 12 and 24 months after stent placement.

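### Quality of life is compared as mean change from baseline with no baseline covariate named, which gives up precision that the collected data could supply

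*Protocol article*

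**What the plan says.** The Statistical methods section of the protocol article sets the form of the comparison for continuous outcomes: "All other continuous outcome measures will be reported as difference in mean improvement between the CS versus the BMS group". For quality of life it then says: "Change in quality of life assessed by the validated questionnaires EQ-5D-5 L" and SF-36 "will be compared between the CS and BMS groups". Neither sentence names a baseline covariate, an analysis of covariance or a repeated-measures model.

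The baseline scores exist. The Follow-up section states: "The patients also receive questionnaires to assess quality of life and cost-effectiveness before stent placement and 6, 12 and 24 months after stent placement". Table 1 shows the same schedule for both instruments. Under Outcome, quality of life is a secondary endpoint at 6, 12 and 24 months.

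**The concern.** A change score subtracts the whole baseline value, which amounts to fixing the regression slope of follow-up on baseline at 1. When the true slope is below 1, this subtracts too much and leaves avoidable noise in the treatment difference. Analysis of covariance estimates the slope from the data.

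The trial is small: 42 patients per arm, with 20% dropout allowed for. What is at stake is the width of the confidence intervals for quality of life, which the Discussion names as something the trial should inform. The baseline measurement that would narrow them is already being collected.

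**Working it through.** **Inputs from the protocol article.** Patients per arm and dropout: "accounting for a 20% dropout rate, 42 participants are required per arm to achieve 80% power with a two-sided alpha of 0.05" (Sample size). Completers per arm: 42 × 0.8 = 33.6, taken as 33. Allocation is 1:1 (Randomization).

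**Inputs that are assumptions.** The correlation r between baseline and follow-up within an arm, and the standard deviations (SDs) at baseline (s_b) and follow-up (s_f). The documents give none of these.

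**Plan's own figure.** There is none for this point, because no sample size or power is stated for quality of life. The 42 per arm was derived for patency (63% against 95%). A pooled z-test on those inputs gives 25 per arm, or 32 after division by 0.8. That mismatch is a separate matter. Here 42 serves only as the number recruited.

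**Step 1: general result.** Per-patient variances, large samples:
- change score: s_b² + s_f² − 2·r·s_b·s_f
- baseline-adjusted: s_f²·(1 − r²)
- difference: (s_b − r·s_f)²

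The difference is a square, so the change score is never the more precise of the two. They tie only when s_b = r·s_f, that is, when the regression slope r·s_f/s_b equals 1.

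**Step 2: equal SDs (assumed), in units of the outcome variance.** The change score has variance 2(1 − r) and the adjusted analysis 1 − r², so the ratio is (1 + r)/2. The last column is a simulation of 8,000 trials per value of r with 33 patients per arm, which includes the cost of estimating the slope.

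| r | Change score | Adjusted | Ratio | Variance cut | Interval narrower by | Simulated ratio |
|---|---|---|---|---|---|---|
| 0.3 | 1.40 | 0.91 | 0.65 | 35% | 19% | 0.68 |
| 0.5 | 1.00 | 0.75 | 0.75 | 25% | 13% | 0.76 |
| 0.7 | 0.60 | 0.51 | 0.85 | 15% | 8% | 0.86 |

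The interval column is 1 − √ratio.

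**Step 3: unequal SDs.** Take s_b = 0.7·s_f (assumed) and s_f = 1:
- r = 0.3: change 0.49 + 1 − 0.42 = 1.07; adjusted 0.91; cut 15%
- r = 0.5: change 0.49 + 1 − 0.70 = 0.79; adjusted 0.75; cut 5%
- r = 0.7: change 0.49 + 1 − 0.98 = 0.51; adjusted 0.51; cut 0%

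**Step 4: what this means at 33 completers per arm.** With equal SDs, an assumed true difference of 0.5 SD and the large-sample variances of Step 2, power for the change score against the adjusted analysis is 40% against 57% (r = 0.3), 53% against 65% (r = 0.5) and 75% against 81% (r = 0.7). At r = 0.5 the difference detectable with 80% power falls from 0.69 SD to 0.60 SD.

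**Step 5: chance baseline imbalance.** Let D be the observed baseline difference between arms and b the regression slope. The change-score estimate equals the adjusted estimate minus (1 − b)·D. Randomization gives D an expectation of zero, so no bias arises. The per-patient variance of the extra term is (1 − b)²·s_b² = (s_b − r·s_f)², exactly the excess in Step 1. Imbalance and lost precision are therefore one effect.

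**The case against.** The strongest reply is that the text names the quantity to be reported and does not rule out covariates. A model for change with baseline as covariate gives the same arm coefficient as a model for the follow-up value with baseline as covariate, and it still reports a difference in mean improvement. The article condenses a fuller document, and covariates for secondary outcomes are often left to the analysis plan. Part of this stands: the article does not forbid adjustment, and a reader should not infer that it commits the trial to an unadjusted analysis. What remains is that the only estimator it names is a difference in mean change, and followed literally that means subtracting baseline and comparing means. A better estimator is available from the same data.

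Three stronger readings are tempting and are not supported:
- **Bias.** A reader might infer that chance baseline differences bias the result, or are a second harm beside lost precision. Step 5 shows neither is so under randomization.
- **Scope.** The wording covers all continuous outcomes, but quality of life is essentially the only one affected. Costs are handled separately, and bodyweight is recorded ("with a visit to the outpatient clinic to assess symptoms and bodyweight") but is not a listed endpoint.
- **A fixed gain.** A reader might take 25% at r = 0.5, equivalent to one third more patients (1/0.75 = 1.33), as an established saving. It needs equal SDs. Patients enter because they have symptoms, so a narrower spread at baseline is plausible, and Step 3 shows how far the gain can shrink.

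**Conclusion.** The point holds as a modest, nearly free improvement to a secondary analysis. The comparison of change is valid, but in large samples it is never more precise than one adjusted for baseline. With equal SDs and r between 0.3 and 0.7, adjustment lowers the variance by 35% to 15%, or about 32% to 14% in the simulation at 33 completers per arm. With a baseline SD of 0.7 of the follow-up SD, the gain is 15% to nil. The direction follows from the algebra; the size rests on correlations and SDs that the documents do not give. The primary patency comparison, its error rate and its power are untouched.

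**What to change.** State in Statistical methods, or in the analysis plan if that is still open, that the between-arm difference in EQ-5D-5L and SF-36 scores at 6, 12 and 24 months is estimated with the baseline score as a covariate. Either an analysis of covariance at each visit or a repeated-measures model will do. Keep mean change per arm as a descriptive summary. Centre terms or the choice of one main visit are not needed for this point.

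The cost is one sentence and one degree of freedom. No new data are required, and no patient is lost compared with the change score, which also needs a baseline value. The Trial status section has 71 of 84 patients included in September 2018 with two years of follow-up, and Data monitoring rules out an interim analysis. On those dates the sentence could be fixed before any comparative results are seen.

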### Harms

Adverse events are defined as any undesirable experience occurring to a subject during the study, whether or not considered related to the implantation of a BMS or CS. A serious adverse event (SAE) is any untoward medical occurrence or effect that at any dose:
Results in deathIs life threatening (at the time of the event)Requires hospitalization or prolongation of existing inpatients’ hospitalizationResults in persistent or significant disability or incapacityIs a congenital anomaly or birth defectAny other important medical event that may not result in death, be life threatening or require hospitalization, may be considered a serious adverse experience when, based upon appropriate medical judgment, the event may jeopardize the subject and may require an intervention to prevent one of the outcomes listed above

All physicians who are involved in the trial are asked to report all adverse events to the coordinating investigator. The coordinating investigator will report the SAEs through the web portal ToetsingOnline (https://www.toetsingonline.nl) of the Dutch Central Committee on Research involving human subjects to the accredited Institutional Review Board that approved the protocol, within 15 days after the coordinating investigator has first knowledge of the serious adverse reactions. Serious adverse events that result in death or are life threatening should be reported expedited. The expedited reporting will occur not later than 7 days after the responsible investigator has first knowledge of the adverse reaction. This is for a preliminary report with another 8 days for completion of the report.

### Auditing

Representatives of the initiating center, Erasmus MC University Medical Center, audit the participating centers during the course of the study. All protocol modifications are communicated to the relevant parties.

### Research ethics approval

The CoBaGI trial is performed in accordance with declaration of Helsinki and the Dutch law regarding research involving human subjects (Wet Medisch wetenschappelijk Onderzoek met mensen (WMO)). The Institutional Review Board of Erasmus MC University Medical Center, Rotterdam, the Netherlands approved the study protocol on 15 October 2013. The boards of the other five Dutch participating centers gave permission for conducting the trial in their center. The CoBaGI trial was registered on 29 April, 2015 at ClinicalTrials.gov with identification number NCT02428582.

### Protocol amendments

Five protocol amendments were approved after initial approval of the CoBaGI protocol by the Institutional Review Board. The subjects of these amendments were the addition of new inclusion centers, the addition of one inclusion criterion and adjustment of the patient information form. The contents of these amendments have been incorporated into this protocol.

